**Fig. 3 Fig3:**
[figure not shown]
Overview of a stereotypical route that may be navigated by a VI end user in Bangkok, using VIS^4^ION with expanded location microservices

### Criteria for discontinuing or modifying allocated interventions {11b}

Principal investigator may terminate or suspend the study under certain circumstances. Circumstances that may warrant termination or suspension include, but are not limited to, unexpected, significant, or unacceptable risk to participants, insufficient compliance to protocol requirements, invaluable or insufficient data, futility determination, and demonstration of efficacy that would warrant stopping.

Participants may withdraw or take back their permission to use and share their health information at any time for this research study. If participants withdraw permission, we will not be able to take back information that has already been used or shared with others.

### Strategies to improve adherence to interventions {11c}

Since subjects will be in the study for a sustained period (for each respective phase), given scheduling requirements, the dedicated research coordinator will clearly communicate expectations to help overcome any potential difficulties. We will make our best attempts to obtain 3 different contact options to ensure that we are able to communicate with the subjects on an ongoing basis.

We will ensure that access to study facilities is aided by route mapping/transportation planning, ensuring the retention of patients given inconvenient geographic logistics from the research site-to-domicile.

Training of clinical and study staff will ensure streamlined communication and avoid miscommunication. A research coordinator at Ratschasuda College will coordinate study assessments while the investigative team will maintain open channels of communication between relevant study facilities for any query at any time point. A clear division of labor and frequent communication will ensure that we retain subjects in the study.

### Relevant concomitant care permitted or prohibited during the trial {11d}

Not applicable. There are no restrictions on concomitant care.

### Provisions for post-trial care {30}

Not applicable. We are not anticipating any post-trial risk.

### Outcomes {12}

The metrics for the entire proposal are detailed as follows:

**Table Tabb:** 

Aims	Aim 1	Aim 2	Aim 3	Aim 4	Aim 5
Tasks	1) Multiple correlation of actual to inferred 3D position (goodness of fit metric comparing the actual and inferred 3D positions) 2) Average error as a function of distance from the center of the 3D map (mapping precision will likely vary as a function of position within the mapped region). The precision metric compares performance consistency to the ideal) 3) Positioning (xy) accuracy and viewing angle accuracy (comparing actual performance to the ideal, i.e., accuracy, shows the size and direction of biases in performance) 4) Beta localization	1) Average changes in normalized path length and variability in path length (i.e., percent change in path length and path variance; comparisons of pre/post path length indicate a potential change in confidence and ability in following a path without getting lost) 2) Average changes in normalized traversal time (i.e., percent change in time; comparison of pre/post traversal times indicates potentially improved general mobility and navigation) 3) For destinations that denote social activities, compute mean difference in time spent on such activities pre to post (comparisons between pre/post means indicate potential changes in levels of social interaction) 4) Pre vs. post fall rates (a comparison to determine if fall rates increase/decrease) 5) Assess QoL using the VFQ25 and WHO-QOLBREF 6) Assess physical function and mobility using IPAQ	Measure acceptability, feasibility, and appropriateness as lumped average scores (5-point Likert scale) across post-interview questionnaire and focus-group discussions	1) Average changes in normalized path length (i.e., percent change in path length) 2) Average changes in normalized traversal time (i.e., percent change in time) 3) For destinations that denote social activities, compute mean difference in time spent on such activities pre-to-post 4) Measure overall activity using total path length/day and total travel time/day 5) Measure BP and BMI pre-topost, and correlate with measures 1–4 6) Pre vs. post fall rates 7) Assess QoL using the VFQ25 and WHO-QOLBREF 8) Assess physical function and mobility using IPAQ 9) We will also conduct a process evaluation according to the Saunders Framework	1) Multiple correlation of actual to inferred 3D position (goodness of fit metric) 2) Average error as a function of distance from the center of the 3D map (mapping precision will likely vary as a function of position within the mapped region) 3) Compare (*t*-test) correlations and (linear model) average error functions between Aims 1 and 5 to show generalizability

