### Trial design {8}

#### Phase 1

Aim 1: Create a “digital twin” of a particular campus (Ratchasuda — a disability college), testing both the performance of the service itself as well as the functional impact of the system.

Aim 2: Assess the ecology of VI students using the wearable, assessing the home range and activity level. A cohort of 20 VI students will use the wearable during navigation (1 week) in two phases: an initial passive phase, during which the wearable will only record location, and then an active phase, during which the location recording will be enhanced with orientation cueing.

Aim 3: Assess the acceptability, appropriateness, and feasibility of the wearable, as a navigation aid for the BLV, using the results of interviews and surveys to implement improvements to the system.

#### Phase 2

Aim 4: We designed an exploratory experiment to assess and monitor our participant’s health-related changes (increased mobility and QoL). This phase is planned as a prospective, randomized crossover, controlled, non-blinded study to compare to evaluate the effectiveness of the wearable for increasing navigation and quality of life. Twenty BLV participants will be randomized to group A (10 participants) and group B (10 participants). During the first 15 days, group A will go through an active phase and then a passive phase for the next 15 days. Reciprocally, group B will go through a passive phase for the first 15 days and then an active phase for the second half of the month.

Aim 5: We will test the generalizability of the new mapping service in a more challenging environment — testing system performance in Bangkok.

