**Fig. 2 Fig2:**
[figure not shown]
Aerial map of Ratchasuda College (RC) at Mahidol University. A route between two on-campus locations is delineated

#### Aim 2

We will recruit a cohort of twenty BLV students currently enrolled in classes at Mahidol University. Students will be asked to don a wearable (bookbag) during all tasks requiring navigation for one week (10 days)**.** Ethograms will be constructed by coding the basic behaviors documented while navigating particular sections of campus, including public transport access points, street crossings, street hazards, e.g., areas with scaffolding, navigation to and through entrances, straight paths (to assess veering), curved paths, and elevation changes, e.g., stairs and ramps. We will collect data on the behavioral components of each situation to understand the effects of the environment on the participant as one moves through campus and the variables that trigger and modify related behaviors [27]. We will describe the mobility phenotype as BLV users interact with a complex range of obstacles in the various areas of campus, cataloging the vastly different reactions and consequences triggered by each. Particular obstacles and campus areas may have a higher likelihood of precipitating mechanical falls, leading to potentially catastrophic injuries. Thus, this process will guide the training of machine learning algorithms based on the specific task to be completed. For example, an intersection crossing near a bus stop for someone with a high degree of veering is particularly precarious; this and other related findings require specific attention and additional safety prompting. We will test navigation assistance (short-term) by comparing the initial five days with the VIS^4^ION system worn in passive mode (acquiring data, providing no assistance/feedback on location and orientation) to the final 5 days with the system worn in active or assistive mode (acquiring data and simultaneously providing assistance/audio feedback).

#### Aim 3

We will ask the same cohort of BLV students enrolled in Aim 2 to participate in focus group discussions (FGD) to assess the acceptability and appropriateness of VIS^4^ION. A research team member will conduct FGDs, each of which will consist of 6**–**8 individuals, and an interpreter will help facilitate the discussion [28].

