Each FGD session will last roughly 60 min and include participants’ perceptions and experiences while navigating the VIS^4^ION system. The FGDs will be guided by pre-determined questions related to general perceptions of the VIS^4^ION system, as well as thoughts on the facilitators and barriers of the intervention. The FGD sessions will be audio-recorded verbatim and later transcribed and translated into English by the research team. During the sessions, the research team member will also take field notes.

#### Aim 4

A cohort of 20 (new) participants will be recruited to assess extended-use benefits over one month. We will create two groups for the randomized crossover design. Each participant will be randomized to either sequence A (10 participants) or sequence B (10 participants). During the first 15 days, group A will go through an active phase and then a passive phase for the next 15 days. Reciprocally, group B will go through a passive phase for the first 15 days and then an active phase for the second half of the month. During the passive phase, the wearable will be maintained in a monitoring mode and simply acquire data, providing no assistance/feedback on location and orientation. During the active phase, the wearable will have an activated assistive mode, i.e., the wearable will acquire data and simultaneously provide assistance/audio feedback. We will evaluate the effectiveness of the wearable for increasing navigation and quality of life. We hypothesize that the VIS^4^ION wearable will improve navigation and quality of life in individuals with visual disabilities.

During the active phase, subjects will complete their daily activities while wearing VIS^4^ION and using the mapping and localization microservice to facilitate wayfinding. Throughout the study we will monitor navigation performance through the same metrics as delineated in Aim 2 [week 2 compared to week 4], as well as to monitor for any falls that may occur (IMU-based alerting); we will also subjectively assess visual function through the 25-Item National Eye Institute Visual Function Questionnaire (VFQ25) [29], physical function and mobility, through the International Physical Activity Questionnaire (IPAQ) [30, 31], and QoL, through the World Health Organization QoL Brief (WHO-QoL-BREF) [32, 33]. The subjective assessments will be performed on day 0 (day of device delivery and initiation) and on the final day of the trial (day 31).

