**Fig. 4 Fig4:**
[figure not shown]
Correlations between ground truth positions and those computed from Pos-Net and Loc-Net (left) and corresponding 2D errors (right)

We have collected a small sample of preliminary data (Fig. 4) to demonstrate the feasibility of these analyses, and that they are capable of demonstrating improvement (green; Loc-Net) relative to our baseline (blue; prior art) methods. There is a clear, qualitative improvement in the green plots, both in precision (left, improved correlation) and accuracy (right, error scatter). Our ability to discriminate between methods will only improve with the larger dataset proposed for this aim.

#### Aim 2

We will use the trained network to predict the real-time pose of a BLV user and create a mobility home range for each participant during both the passive and active phases of this initial pilot. We anticipate that route planning will improve through more efficient wayfinding in the active phase, when users have a more comprehensive understanding of the local environment (spatial cognition). We will extract paths between pre-selected pairs of locations during the active and passive phases (e.g., residence to classroom building) traversed in the pre (first 5 days) and post (last 5 days) periods to evaluate our predictions, measuring:Average changes and variability in path length (i.e., percent change in path length [difference test based on binomial distribution] and path variance [F-test of variances])Average changes in normalized traversal time (i.e., percent change in time [difference test based on binomial)For destinations that denote social activities, estimate the difference in time spent on such activities pre to post [time difference based on Wilcoxon signed rank test].Pre vs. post fall rates using an exponential waiting-time model of time between falls [Poisson rate of falling]Total area covered on an hourly, daily, and weekly basis to assess a home range

#### Aim 3

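### Aim 4 activity, social time and falls are recorded only by the device under test, and no wear instruction or worn-time measure keeps the passive and active phases comparable

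*Protocol article*

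**What the plan says.** The device supplies the data. Under Trial design {8}, Phase 1 has "an initial passive phase, during which the wearable will only record location". Under Intervention description {11a}, Aim 4, falls are picked up by alerts from the device's inertial sensor. The article names no second source for path, travel time, area or time at social destinations.

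In the Aim 4 passive phase, "the wearable will be maintained in a monitoring mode and simply acquire data, providing no assistance/feedback on location and orientation". The section on who will be blinded {17a} says participants are not blinded.

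Wear is described differently in the two aims:

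- **Aim 2:** one instruction covers both modes: "Students will be asked to don a wearable (bookbag) during all tasks requiring navigation for one week (10 days" (the parenthesis closes there). The same paragraph then describes the system as worn in each mode.
- **Aim 4:** "During the active phase, subjects will complete their daily activities while wearing VIS^4^ION". There is no matching sentence for the passive phase.

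For the outcomes, the table under Outcomes {12} lists for Aim 4 "Measure overall activity using total path length/day and total travel time/day", together with the pre-to-post difference in social time and fall rates. Under Statistical methods {20a}, Aim 2 adds "Total area covered on an hourly, daily, and weekly basis to assess a home range". Aim 4 takes over the Aim 2 navigation metrics by reference. Fall rates use a Poisson waiting-time model whose exposure term, delta t, is not defined as worn or elapsed time.

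The adherence section {11c} deals with scheduling, contact and transport. For example, "the dedicated research coordinator will clearly communicate expectations to help overcome any potential difficulties". It does not mention wearing the device.

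**The concern.** A trip made without the backpack leaves no trace in the data. If participants wear the pack less when it does nothing for them, the passive phase yields smaller recorded totals even when they move about just as much. The shortfall would look like greater activity and more social time in the active phase, and in Aim 2 like a wider home range. Objectives {7} predicts more activity and a wider home range.

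The crossover does not protect against this. Randomising the sequence balances period effects, but wear that depends on the mode travels with the mode in both sequences.

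Nothing else in Aim 4 offers a check by phase. The visual-function, activity and quality-of-life questionnaires do not depend on wear, but they are given only on day 0 and day 31, so they cannot separate active from passive. The outcome table also correlates blood pressure and BMI with the movement measures, which would carry any error further.

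**Working it through.** **Model.** Let T be the true daily total in a mode and w the share of that movement made with the pack on and recording. The recorded total is T × w, so

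recorded active / recorded passive = (T_A × w_A) / (T_P × w_P).

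With no true effect, T_A = T_P and the ratio reduces to w_A / w_P. The article gives no wear data, so every wear share below is an assumption.

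| Assumed wear, active vs passive | Ratio | False difference |
|---|---|---|
| 85% vs 80% | 0.85/0.80 = 1.06 | +6% |
| 90% vs 70% | 0.90/0.70 = 1.29 | +29% |
| 95% vs 60% | 0.95/0.60 = 1.58 | +58% |

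**Scale against the plan's own power statement.** The Sample size section claims power of at least 0.8 with 20 subjects when initial path lengths are 40% shorter than with the aid, with a standard deviation of length ratios up to 2.5, on the log scale. Alpha and sidedness are not stated. Reading 2.5 as a multiplicative standard deviation and taking a one-sided 0.05 normal test:

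- |ln 0.6| = 0.511 and ln 2.5 = 0.916
- 0.511/0.916 × √20 = 2.49
- 2.49 − 1.645 = 0.85, and Φ(0.85) = 0.80

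This reproduces the stated 0.8. A two-sided normal test gives 0.70. The figure itself is not in dispute and serves only as a yardstick.

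Passive wear at 60% of active wear would make recorded passive totals 40% shorter with no true effect, which equals the design effect. The chance of a false benefit, with r = passive wear / active wear, is Φ(|ln r|/0.916 × √20 − 1.645):

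| r | Chance of a false benefit |
|---|---|
| 0.9 | 0.13 |
| 0.8 | 0.29 |
| 0.7 | 0.54 |
| 0.6 | 0.80 |

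The nominal rate is 0.05. Applying the Phase 1 path-ratio standard deviation to Aim 4 daily totals is a further assumption, so these figures show order of magnitude only.

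**Falls.** Suppose the true fall rate is equal in both modes and falls are seen only while the pack is worn. If delta t is elapsed time, the recorded active-to-passive rate ratio is again w_A / w_P, so active mode looks worse. If delta t is worn recording time, the factor cancels. The direction is opposite to that for activity, and the bias depends on a definition the article leaves open.

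**Why dividing by worn hours is not a full answer.** Where the pack is put on for navigation, worn hours are largely travel time. If the device truly doubled travel, worn hours would also roughly double, and travel per worn hour would be 2/2 = 1. A real benefit would vanish.

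**The case against.** Several stronger readings are tempting and are not supported by the text.

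- A reader might infer that the plan fixes a calendar-day denominator and scores unworn trips as zero. It says neither. The outcome is a total per day, and area is also given hourly. The section on non-adherence and missing data {20c} assumes data missing at random, with Bayesian imputation if that fails. It does not identify unworn time as missing, so the gap remains, but it does not instruct zero-filling.
- A reader might infer that wear instructions differ by mode throughout. In Aim 2 they are the same. In Aim 4 there is an omitted sentence, not a different rule, and the section on comparators {6b} speaks of extended use in both phases.
- A reader might infer that wear will be lower in passive mode. No passage says so. The Background does cite low long-term use of mobility devices, which makes non-wear foreseeable but says nothing about a difference between modes.
- A reader might infer that fall rates are biased as written. The model has an exposure term that could be worn time; it is simply undefined.

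Adherence is also monitored more than section {11c} suggests. Data are audited after each session, checks and reports are regular, and the process evaluation covers fidelity and exposure received. None of this is tied to the outcome measures.

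Aim 4 is called exploratory, and daily activity is one of nine listed items. Valid-day thresholds are often left to an analysis plan. These points lower the severity. They do not supply the missing Aim 4 wear instruction or link the daily totals to recording time.

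**Conclusion.** The concern holds in limited form. In Aim 4 the recorder is the intervention, the passive wear instruction is not stated, and no passage relates daily totals or social time to time worn. Any difference in wear between modes would pass one-for-one into the active-passive contrast, and randomised order would not remove it. Under assumed wear of 85% against 80% the false gain is 6%, and under 90% against 70% it is 29%. This rests on equal true behaviour in both modes and on recording proportional to wear.

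Aim 2 area and social time share the risk despite the common instruction, because participants may still follow it less in passive mode. Path length and traversal time between pre-selected pairs of points are much less exposed, since they are measured within recorded trips.

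This should be fixed, and the article says enrolment had not begun. It does not invalidate the design.

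**What to change.** 1. In Intervention description {11a}, Aim 4, state that the wear instruction is identical in the active and passive phases.
2. Derive worn, recording time per day from the device logs. Report it by mode beside every activity, area and social-time result.
3. Keep daily totals as the main measure. Treat days without adequate recording as missing, not as low activity, using one minimum-wear rule set in advance for both modes, and report the number of days excluded by mode. Show per-worn-hour results as a sensitivity analysis only. They should not decide whether a gain may be claimed, because worn hours partly reflect true activity.
4. Define delta t in the fall-rate model as worn recording time. Also reconcile the Aim 5 statement that inertial-sensor signals were not used earlier with the Aim 4 use of that sensor for falls, so that the source of fall data is clear.
5. Qualify any claim of greater activity if worn time differs materially between modes.

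The cost is a few sentences of protocol and analysis text and one derived variable. Some days will be excluded, and a genuinely quiet day may be hard to tell from an unworn one, which is why exclusions should be shown by mode.

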
### Participant timeline {13}

**Table Tabc:** 

				**Study period**					
	**Enrolment**	**Allocation**		**Post-allocation**					**Close-out**
**Timepoint (Y/M)**	***Y1/M3***	**0**	***Y1/M9***	***Y2/M3***	***Y2/M12***	***Y4/M6***	***Y5/M6***	***Y5/M9***	***Y5/M12***
**Create and establish DSMB**	X								
**Develop study protocol and SOP for testing and staff training**	X								
**Finalize ICF and recruitment materials/IRB approval**	X								
**Allocation**		X							
**Participant enrollment**	X	X	X	X	X	X	X	X	
**Aim 1**			X						
**Aim 2**				X					
**Aim 3**					X				
**Aim 4**						X			
**Aim 5**								X	
**Concurrent data processing for all Aims**			X	X	X	X	X		
**Preliminary data complete**				X	X	X	X		
**Preliminary data analyses, presentations, manuscripts**				X	X	X	X	X	
**Final statistical analyses, presentations, manuscripts**								X	X

*DSMB* Data Safety Monitoring Board, *SOP* standardized operating procedures, *ICF* informed consent form, *IRB* Institutional Review Board, *M* month

### Sample size [1]

A total of 40 visually impaired subjects will be recruited over the 5 years of this proposed research program. In the first phase, we will focus on demonstrating that travel has improved, using a metric based on the ratio of path length. Path length is a non-normal variate, right-skewed, and must be transformed to satisfy the constraints of a parametric statistical test.

We use log-transformed path-length ratios for the power calculation, by which we determined that, with a statistical power of at least 0.8, we will be able to detect a path-length difference for 20 subjects in which the initial path lengths are 40% shorter than those taken when using the navigation aid, assuming a standard deviation of length-ratios no larger than 2.5.

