We will also use the Saunders Framework [34] to conduct a process evaluation of the intervention. This process evaluation will monitor program implementation to better understand the relationship between intervention components, process/implementation measures, and health outcomes. The Saunders Framework provides a systematic approach for assessing key process measures across several domains. This approach will generate both formative and summative data [35–37]. A combination of quantitative and qualitative approaches will be utilized, including observation forms, checklists, surveys, record review, FGDs, and KIIs (key informant interviews). Study participants, clinical staff, and study and clinical encounter forms will be the sources of data. Members of the research team will conduct semi-structured interviews with students’ post-experiment; the session will be audio-recorded verbatim. Interview audio-recordings will be transcribed and translated into English by the research team. Special emphasis will be placed on Thai cultural and lifestyle preferences.

#### Aim 5

We will recruit a cohort of twenty BLV students to assess the generalizability of our previously described techniques. We will extend our mapping/localization program from the RC campus to a 12-block portion of Bangkok (Fig. 3), giving students the opportunity to more easily access the vibrant city center. To address the challenge of image-based mapping/localization in a large-scale environment, we will divide the large-scale territory to be mapped into smaller territories, roughly breaking down the proposed area of study into one block region. We intend to add a coarse localization tool, using GPS and the embedded IMU in the camera, to efficiently narrow down our search space from the entire territory to a smaller regional city block, subsequently we can deploy our image-based techniques.

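### The sample-size section states its effect in the wrong direction, its power of 0.8 holds only under favourable unstated choices and for a different test from the one planned, and its total of 40 does not match the cohorts described

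*Protocol article*

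**What the plan says.** The Sample size section sets out to show that travel improves in the first phase, using a ratio of path lengths analysed on the log scale so that a parametric test is valid. It claims that "with a statistical power of at least 0.8", "we will be able to detect a path-length difference for 20 subjects", where "initial path lengths are 40% shorter than those taken when using the navigation aid, assuming a standard deviation of length-ratios no larger than 2.5". It gives no alpha, sidedness or named test, and does not say on which scale the 2.5 is measured.

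Statistical methods {20a}, Aim 2, takes routes between location pairs chosen in advance, passive first five days against active last five days, in the same students. Its prediction is: "We anticipate that route planning will improve through more efficient wayfinding in the active phase". For path length the planned analysis reads "percent change in path length [difference test based on binomial distribution" (closing bracket omitted).

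On numbers, the Sample size section says: "A total of 40 visually impaired subjects will be recruited over the 5 years of this proposed research program". The Recruitment section repeats forty. Intervention description {11a} has twenty students for Aim 2, the same students for Aim 3, twenty participants marked as new for Aim 4, and for Aim 5: "We will recruit a cohort of twenty BLV students to assess the generalizability of our previously described techniques".

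**The concern.** Three things do not fit together.

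- **Direction.** If the initial (unaided) path is 40% shorter than the aided one, the aid lengthens the route. Between fixed endpoints that is deterioration. A one-sided test set up in the stated direction would look for harm and call it improvement.
- **Power.** A reader who assumes the usual two-sided 5% level and a paired t-test on log ratios cannot recover 0.8 from the stated inputs. The test listed for Aim 2 is not the test that was powered.
- **Count.** Three cohorts of twenty add up to 60, not 40, unless one of them is reused.

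At stake are how an inconclusive path-length result in Aim 2 may be read, which direction of change counts as success, and whether the approved enrolment covers Aim 5.

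**Working it through.** **Inputs.** From the Sample size section: n = 20, ratio 0.6 (initial over aided), SD 2.5, log scale. From Aim 2: each subject is measured in both phases, so the comparison is paired. Assumed, because not stated: 5% level, one- or two-sided; 2.5 read first as a multiplicative SD.

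**Effect size.** |ln 0.6| = 0.511; ln 2.5 = 0.916; d = 0.511/0.916 = 0.5575; d√20 = 2.493.

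**Reproducing the stated figure.** Normal approximation, one-sided 5%: Φ(2.493 − 1.645) = Φ(0.848) = 0.802. Required n = ((1.645 + 0.842)/0.5575)² = 19.9, so 20. Both stated figures are recovered.

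**Same inputs, other 5% tests.** Two-sided normal approximation: Φ(2.493 − 1.960) = 0.703. Noncentral t with 19 df: 0.776 one-sided and 0.658 two-sided. For 0.80 the t-test needs 22 subjects one-sided and 28 two-sided.

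**Other readings of the 2.5 (t-test, n = 20).**

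| Reading of the SD | Log SD | Two-sided | One-sided |
|---|---|---|---|
| Multiplicative | 0.916 | 0.66 | 0.78 |
| SD of the natural-log ratios | 2.5 | 0.14 | 0.22 |
| Arithmetic SD, lognormal, median 0.6 | 1.244 | 0.41 | 0.55 |
| Arithmetic SD, lognormal, median 1/0.6 = 1.67 | 0.856 | 0.72 | 0.82 |

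The largest two-sided figure is 0.76, from the normal approximation to the last row. No two-sided 5% reading tried reaches 0.80.

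**What 20 subjects can detect.** With the two-sided t-test, 0.80 needs d = 0.660. At log SD 0.916 that is exp(−0.660 × 0.916) = 0.546, about a 45% reduction. For a 40% reduction, the multiplicative SD can be at most exp(0.511/0.660) = 2.17.

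**Direction.** Initial/aided = 0.6 means aided/initial = 1.67, so routes are 67% longer with the aid. Stating instead that aided routes are 40% shorter keeps |ln 0.6|, so power on the multiplicative reading is unchanged. The correction is not automatic: if initial routes 40% longer was meant, the effect is ln 1.4 = 0.336, d = 0.367, and t-test power falls to 0.34 two-sided or 0.48 one-sided.

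**Planned test.** Reading the binomial test as a sign test on 20 subjects (assumption), the chance that a subject moves in the hypothesised direction is Φ(0.5575) = 0.711. Under the null, P(X ≥ 14) = 0.058 and P(X ≥ 15) = 0.021, so the cut is 15 of 20 at 5%, one- or two-sided. Power = P(X ≥ 15 | 20, 0.711) = 0.46.

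**Count.** Aims 2 and 3: 20. Aim 4: 20 new. Aim 5: 20. Sum 60 if Aim 5 is a separate cohort; 40 if it reuses earlier participants.

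**The case against.** **Power.** A reader might infer that 0.8 is an arithmetic error, refuted by the plan's own inputs. The document does not support that. It states neither alpha nor sidedness, two-sided 5% is an outside assumption, and one-sided 5% with a normal approximation returns both 0.80 and 20. The hypothesis is directional, so a one-sided test is plausible, and a condensed article may leave such details to a fuller document. That stands. What remains is that the figure is fragile: the normal approximation treats the SD as known, and the t-test with the same inputs misses 0.80 even one-sided.

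**Binomial test.** The article fixes neither its unit (subject or route) nor its sidedness, so 0.46 is conditional. The mismatch between a powered parametric test and a planned binomial one is in the text regardless.

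**Direction.** The phrase may simply be swapped, and the Objectives also expect a wider home range, so more travel can count as benefit in this programme. But Aim 2 lists area covered as a separate measure, and the Outcomes table links path length to following a route without getting lost. The home-range expectation does not rescue the sentence.

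**Count.** A reader might infer that the true total is 60. This is not proven: Aim 4 participants are marked as new and Aim 5 participants are not, so reuse is possible. Against that, the article says so when it reuses a cohort (Aim 3), uses the verb recruit for Aim 5, and shows enrolment continuing into the Aim 5 column of the timeline. It is an unresolved inconsistency. The Aim 5 endpoints in the Outcomes table are localisation metrics, so reuse need not undermine them.

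**Conclusion.** The concern holds in this form.

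- The direction of the design effect is wrong as written. This rests on the text alone, with no assumption about alpha or SD.
- The stated power is attainable but only under favourable, unstated choices: 0.802 with one-sided 5%, normal approximation and multiplicative SD, or 0.82 with a one-sided t-test if 2.5 is the arithmetic SD of a lognormal ratio with median 1.67. Under a two-sided 5% paired t-test with log SD ln 2.5 it is 0.66.
- The powered test and the planned test differ. Power is about 0.46 if the latter is a subject-level sign test.
- The total of 40 and the three cohorts of twenty are unreconciled; neither 40 nor 60 can be confirmed from the article.

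**What to change.** 1. State the effect as paths 40% shorter with the aid. On the multiplicative reading of the SD this leaves power unchanged.
2. State alpha, sidedness and the scale of the SD, and give the power that follows. With two-sided 5%, a paired t-test and log SD ln 2.5, that is 0.66 for a 40% change, with 0.80 reached at about a 45% change.
3. In Aim 2, use the paired test on log ratios for path length, or restate the power for the binomial test with its unit and sidedness given.
4. In the Sample size and Recruitment sections, either give the total as 60 or say that Aim 5 re-enrols earlier participants.

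The cost is wording and a less favourable stated power. If the total is 60, the approved enrolment number must be updated, but nobody is added beyond the cohorts already described. The article reports that enrolment had not begun.
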